**Follow up**

The following variables were collected during follow-up visits: weight, waist circumference, blood pressure, International Physical Activity Questionnaire [4], Food knowledge assessment, Food craving inventory, Three Factor Eating Questionnaire [6], EQ-5D, use of health services questionnaire, adverse events, participant feedback and medication use.

In the intervention arm the following were collected during the 8-week intervention phase: pedometer use, food diary use, and adherence to weekly tasks (e.g. increase fruit and vegetable intake, increase exercise, monitoring television and computer use).

**Timing of data collection**

The recruitment period was: September 2012– January 2014 (17 months) and the study sessions were conducted as follows:

Week -1: Screening

Week 0: Randomisation

Weeks 1-8: Intervention group – 8 weekly sessions

Control group – 4 fortnightly sessions

Months 3-12: Intervention group – 10 monthly follow-up sessions

Control group – 6 and 12 month follow-up sessions only

**Database**

Description

Data were entered into the online database, ‘Oracle Database version 11’, hosted at the Barts Cancer Centre. The Electronic Data Capture forms are web based and built using Java with data validation in JavaScript (Java framework Struts 2).

Data quality

When recruitment and follow-up are complete, the study team will clean the data in the following way: values for each variable will be sorted, and those at the extremes will be checked to ensure that they are within the expected range.

Source data verification will also be conducted: a random sample of 10% of CRFs will be selected, and a member of QA team (PCTU) will compare all written entries with those entered onto the main study database. The pre-specified data quality target is ≤ 2% discrepancy rate between entries in the CRF and the electronic database. If an error is found in >2% of entries, the quality target for data entry will not have been met, and all CRF data will be cross-checked against data in the study database. (This would be done by counting up the maximum number of data items that could be entered for a patient on each of the CRFs, ignoring free text fields. Errors will be tallied and these would include any items that were inadvertently missed out.)

Derived and computed variables

All derived and computed variables will be documented in the analysis programmes.

1. **GENERAL ISSUES FOR STATISTICAL ANALYSIS**

**General analysis principles**

The main analysis for each outcome will use intention-to-treat (ITT) principles, meaning that all participants with a recorded outcome will be included in the analysis, and will be analysed according to the treatment group to which they were randomised. More information on which participants will be included in each analysis is available in the section below. All p-values will be two sided, and the significance level is set at 5%.

Analyses for all outcomes will be presented as:

- The number of participants included in the analysis, by treatment group;
- A summary measure of the outcome, by treatment group (e.g. mean (SD) for continuous outcomes, number (%) for binary outcomes);
- A treatment effect, with a 95% confidence interval;
- A two-sided p-value.

All analyses will account for clustering by group in the intervention arm, and clustering by nurse in the control arm. Each patient will be defined as belonging to a cluster, defined by which group they belonged to if they were in the intervention arm, and which nurse they were treated by if they were in the control arm. This variable will be included as a random intercept in a mixed-effects regression model. This analysis assumes the intraclass correlation coefficient is the same between groups in the intervention arm as it is between nurses in the control arm. The Kenward-Roger degree-of-freedom correction will be employed for all linear mixed-effects models.

All analyses will adjust for baseline weight, age, gender, ethnicity (White British, White other, Black, Asian, Mixed, or other), smoking status (smoker vs. non-smoker) and GP practice (Lawson vs. Barkantine) as covariates in a regression model. Outcomes which are measured at baseline will also be adjusted for the value of the outcome at baseline (this includes weight, BMI, waist circumference, systolic and diastolic blood pressure, Food Craving Inventory, Food Knowledge Assessment, Three Factor Eating Questionnaire, and IPAQ). Continuous covariates (baseline weight, age) will be assumed to have a linear association with outcome. Binary and categorical covariates (gender, ethnicity, smoking status, and GP practice) will be included in the regression model using indicator (dummy) variables. Missing baseline data will be accounted for using mean imputation.

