**Outcome measures**

Primary outcomes

The primary outcome measure is the change in weight (in kg) at 12 months post-randomisation.

Secondary outcomes

- Change in weight (in kg) at 1, 2, and 6 months post-randomisation.
- Change in BMI at 1, 2, 6 and 12 months post-randomisation. BMI is calculated as weight (in kg) divided by the square of height (in metres). The height measured at screening will be used for each follow-up assessment.
- Change in waist circumference (in cm) at 2, 6 and 12 months post-randomisation.
- Change in systolic blood pressure (mmHg) at 2, 6 and 12 months post-randomisation.
- Change in diastolic blood pressure (mmHg) at 2, 6 and 12 months post-randomisation.
- Change in the Food Craving Inventory score (Frequency domain) at 1, 2, 6, and 12 months post-randomisation.
- Change in the Food Craving Inventory score (Strength domain) at 1, 2, 6, and 12 months post-randomisation.
- Change in Food Knowledge Assessment Questionnaire score at 2, 6, and 12 months post-randomisation.
- Change in the Three Factor Eating Questionnaire score (Cognitive Restraint domain) at 2, 6, and 12 months post-randomisation.
- Change in the Three Factor Eating Questionnaire score (Uncontrolled Eating domain) at 2, 6, and 12 months post-randomisation.
- Change in the Three Factor Eating Questionnaire score (Emotional Eating domain) at 2, 6, and 12 months post-randomisation.
- Change in the International Physical Activity Questionnaire (IPAQ) score (MET-minutes/week domain) at 2, 6, and 12 months post-randomisation.
- Change in the International Physical Activity Questionnaire (IPAQ) score (Sitting domain) at 2, 6, and 12 months post-randomisation.
- Proportion of participants losing 5% of body weight at 2, 6, and 12 months post-randomisation.
- Proportion of participants losing 10% of body weight at 2, 6, and 12 months post-randomisation.

Scoring details for the Food Craving Inventory, the Food Knowledge Assessment Questionnaire, the Three Factor Eating Questionnaire, and the International Physical Activity Questionnaire are available in Appendix 2.

Weight, BMI, waist and blood pressure outcomes were measured by researchers who were blind to treatment arm. These researchers were affiliated with the trial team, but were involved only in collecting outcomes during follow-up, and had no role in providing the intervention, and no contact with patients other than whilst collecting follow-up measurements.

1. **STUDY METHODS**

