**Missing data for outcomes**

For outcomes that are measured at multiple time points during follow-up, we have based our analysis strategy on that proposed by White et al 2011[7]. To deal with incomplete data (i.e. when patients have missing data at one of the follow-up time points) we will:

1. Attempt to follow up all randomised patients even if they withdraw from the study
2. Perform a main analysis of all observed data that are valid under a plausible assumption about the missing data
3. Perform sensitivity analyses to explore the effect of departures from the assumptions made in the main analysis
4. Account for all randomised participants, at least in the sensitivity analyses

We will therefore (a) include all patients with at least one post-randomisation assessment (i.e. if they have recorded data for at least one follow-up time point) in the analysis; (b) use mixed-effects models adjusted for baseline covariates, which assumes that the data are missing-at-random (i.e. they are missing based on their observed outcome at other time-points, and other patient characteristics); and (c) perform sensitivity analyses under other missing data assumptions (e.g. that patients who were lost-to-follow-up gained more weight than patients who remained in the trial).

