**Analysis of primary outcome**

The primary outcome (change in weight at 12 months post-randomisation) will be analysed using a mixed-effects linear regression model. The model will include change in weight at 1, 2, 6 and 12 months as outcomes.

The model will include a random intercept for ‘cluster’ (group or nurse, depending on treatment arm). The correlation between observations at different time points from the same patient (1, 2, 6, and 12 months) will be modelled using an unstructured correlation structure. The model will be estimated using restricted maximum likelihood (REML). Treatment arm, time point (month 1, 2, 6, or 12), and the interaction between treatment arm and time point will be included in the model as fixed factors. Time point will be included as an indicator variable. The covariates listed in section 5 will also be included in the model as fixed factors.

The analysis will be implemented in Stata as follows:

mixed outcome treatment##time covariates || cluster_id:, || ///

patient_id:, noconstant residuals(unstructured, t(time)) stddev reml dfmethod(kroger)

If this model fails to converge, we will run the model again using the correlation structure

*residuals(ar 2 , t(time))*. If the model still fails to converge, we will use *residuals(ar 1 , t(time))*.

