*Change in Food Knowledge Assessment at 2, 6 and 12 months*

These outcomes will be analysed using the same method as change in weight at 6 and 12 months. The baseline value of food knowledge will also be as a covariate in the model. Food Knowledge Assessment measurements at 2, 6, and 12 months will be included in the model.

*Change in Three Factor Eating Questionnaire (Cognitive Restraint domain) at 2, 6 and 12 months*

These outcomes will be analysed using the same method as change in weight at 6 and 12 months. The baseline value of the Three Factor Eating Questionnaire (Cognitive Restraint domain) will also be included as a covariate in the model. Cognitive Restraint domain measurements at 2, 6, and 12 months will be included in the model.

*Change in Three Factor Eating Questionnaire (Uncontrolled Eating domain) at 2, 6 and 12 months*

These outcomes will be analysed using the same method as change in weight at 6 and 12 months. The baseline value of the Three Factor Eating Questionnaire (Uncontrolled Eating domain) will also be included as a covariate in the model. Uncontrolled Eating domain measurements at 2, 6, and 12 months will be included in the model.

*Change in Three Factor Eating Questionnaire (Emotional Eating domain) at 2, 6 and 12 months*

These outcomes will be analysed using the same method as change in weight at 6 and 12 months. The baseline value of the Three Factor Eating Questionnaire (Emotional Eating domain) will also be included as a covariate in the model. Emotional Eating domain measurements at 2, 6, and 12 months will be included in the model.

*Change in International Physical Activity Questionnaire (MET-minutes/week domain) at 2, 6 and 12 months*

These outcomes will be analysed using the same method as change in weight at 6 and 12 months. The baseline value of the MET-minutes/week domain will also be included as a covariate in the model. MET-minutes/week domain measurements at 2, 6, and 12 months will be included in the model.

*Change in International Physical Activity Questionnaire (sitting domain) at 2, 6 and 12 months*

These outcomes will be analysed using the same method as change in weight at 6 and 12 months. The baseline value of the sitting domain will also be included as a covariate in the model. Sitting domain measurements at 2, 6, and 12 months will be included in the model.

*Proportion of participants losing 5% of body weight at 2, 6, and 12 months*

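### The SAP does not say whether a missing baseline is imputed before the change score is formed; unless it is, participants with a recorded follow-up are lost from the continuous secondary analyses, against the SAP's own inclusion rule

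*SAP*

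**What the plan says.** Three parts of the SAP bear on this.

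- **Who is analysed.** General analysis principles states that "all participants with a recorded outcome will be included in the analysis". Missing data for outcomes is more specific: the analysis will "include all patients with at least one post-randomisation assessment (i.e. if they have recorded data for at least one follow-up time point) in the analysis". Neither sets a condition on baseline.
- **What is modelled.** Outcome measures defines the continuous secondary outcomes as change, for example "Change in the Food Craving Inventory score (Frequency domain) at 1, 2, 6, and 12 months post-randomisation" and "Change in Food Knowledge Assessment Questionnaire score at 2, 6, and 12 months post-randomisation". For weight, Analysis of primary outcome makes change the dependent variable: "The model will include change in weight at 1, 2, 6 and 12 months as outcomes". Analysis of secondary outcomes applies the same method to the others. Under headings that name a change, however, it says that *measurements* at each visit enter the model.
- **How baseline is used.** General analysis principles says "Outcomes which are measured at baseline will also be adjusted for the value of the outcome at baseline". Analysis of secondary outcomes repeats this outcome by outcome, for example "The baseline value of the Three Factor Eating Questionnaire (Cognitive Restraint domain) will also be included as a covariate in the model". The covariate paragraph ends with "Missing baseline data will be accounted for using mean imputation". The SAP does not say whether that value also serves to derive the change. The Database section leaves derived variables to the analysis programmes.

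**The concern.** A change score needs two values. If mean imputation fills only the covariate, a participant with a follow-up questionnaire and no baseline questionnaire has a covariate but no outcome, and the model drops the record. The imputation rule then does nothing for the outcome's own baseline, and the inclusion rule is not met. Two programmers could follow the SAP faithfully and report different analysis sets.

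What is at stake is mainly adherence to the inclusion rule, plus some precision for the questionnaires and blood pressure, in a trial that already assumes 50% loss at one year. Weight and BMI are little exposed, because Appendix 1 records weight at both the screening and the randomisation sessions. The primary outcome is therefore hardly touched.

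**Working it through.** The SAP gives no figure for missing baselines, so there is none to reproduce. The inputs from Sample size determination are 330 participants, 2:1 allocation and 50% available at one year. The missing-baseline share *m* and the baseline/follow-up correlation *ρ* are assumptions.

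**1. Change and follow-up value are the same model.** Let Y_t be the follow-up value at visit t, B the outcome's own baseline and T the arm. The change model is

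Y_t − B = a_t + d_t·T + γ·B + other terms.

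Adding B to both sides gives

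Y_t = a_t + d_t·T + (γ + 1)·B + other terms.

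The fixed-effect columns and residuals are unchanged, so d_t and its standard error are unchanged and only the baseline slope moves, by 1. A simulated three-visit data set (unstructured within-patient covariance, cluster intercept, 276 participants with a baseline) gave effects of −2.573, −1.732 and −1.769 at 2, 6 and 12 months from both models. The standard errors were 0.591, 0.636 and 0.706 from both. The baseline slope was −0.473 for change and 0.527 for follow-up value.

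**2. If the baseline is imputed before subtraction, nobody is lost.** In the same data set with 10% of baselines missing, filled with the mean over both arms, change from the imputed baseline kept 311 participants. Its effects were −2.375, −2.029 and −1.604. The follow-up value with the imputed covariate kept the same 311 and gave the same effects and standard errors.

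**3. If only the covariate is imputed, participants are lost.** Expected at 12 months: 330 × 0.5 = 165. Lost at *m* = 5%, 10% and 20%: 165 × 0.05 = 8.25, 165 × 0.10 = 16.5, 165 × 0.20 = 33.

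**4. Effect on precision.** Take one visit, no clustering, and baselines missing independently of everything else. Dropping leaves n(1 − m) participants with residual variance σ²(1 − ρ²). Keeping leaves n participants. A share m of them, with baseline set to the mean, has residual variance σ², so the average is σ²[1 − ρ²(1 − m)]. The variance ratio, drop to keep, is approximately

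R = (1 − ρ²) / {(1 − m)[1 − ρ²(1 − m)]}.

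For example, ρ = 0.5 and m = 0.10 give 0.75 / (0.90 × 0.775) = 1.075.

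| ρ | m = 5% | m = 10% | m = 20% |
|---|---|---|---|
| 0.3 | 1.05 | 1.10 | 1.23 |
| 0.5 | 1.04 | 1.08 | 1.17 |
| 0.7 | 1.00 | 1.01 | 1.05 |
| 0.8 | 0.97 | 0.94 | 0.92 |
| 0.9 | 0.87 | 0.78 | 0.67 |

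Simulated trials gave about 1.03 to 1.22 at ρ = 0.3 to 0.5 and 1.01 to 1.04 at 0.7, close to the formula. Setting R = 1 gives ρ² = 1/(2 − m), so the break-even ρ is 0.716, 0.725 and 0.745 at m = 5%, 10% and 20%. Above it, keeping these participants costs precision.

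**5. Where step 1 fails.** It needs the outcome's own baseline in the model. For the Food Craving strength domain, Analysis of secondary outcomes names the baseline of the frequency domain, against General analysis principles. With that covariate, a simulated 12-month effect was −2.07 on change and −1.44 on follow-up value, so the two forms no longer agree.

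**The case against.** A reader might infer that the SAP excludes these participants outright. It does not say so. The imputation sentence speaks of baseline data without limiting it to covariates, and imputing before subtraction is the reading that best fits the inclusion rule. Under it nobody drops out, and step 2 shows that the proposed change would alter nothing. The word *measurements* in the secondary-outcome models can even be read as follow-up values, which is what is proposed here. All of this stands, so exclusion is conditional. What remains is that the sentence sits in the covariate paragraph, the outcomes are defined as change, and no text links the two.

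A reader might also infer that keeping everyone always helps, or that the estimates become the same whoever is included. Neither holds. Step 4 shows a loss of precision at high correlation, and the identity in step 1 is for the same participants only; adding participants changes the estimate.

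Finally, the missing rate may be small. Waist and blood pressure are taken at the randomisation session (Appendix 1), and the questionnaires are administered at baseline. That is a fair reason to rank the point low. It does not settle which analysis set is meant.

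**Conclusion.** The point holds in conditional form. The SAP leaves open whether an imputed baseline is used to form the change. If it is not, participants with a recorded follow-up are dropped from the questionnaire and blood-pressure analyses, contrary to the SAP's own inclusion rule.

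Assuming 5% to 20% of baselines missing at random, the variance of the treatment effect rises by about 3% to 22% at a correlation of 0.3 to 0.5, and by about 1% to 4% at 0.7. With no missing baselines there is no difference. Above a correlation of roughly 0.72 to 0.75 the direction reverses. For a measure that tracks closely over time, plausibly waist, keeping everyone serves the inclusion rule rather than precision.

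These sizes rest on assumed rates and correlations that the SAP does not give. No bias in the treatment effect is shown, and the primary outcome is little exposed.

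**What to change.** In General analysis principles and Analysis of secondary outcomes:

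1. First correct the Food Craving strength model so that it adjusts for the strength-domain baseline.
2. For the questionnaire and blood-pressure outcomes, state that the follow-up value at each visit is the dependent variable and that the outcome's own baseline, mean-imputed where missing, is a covariate. All other terms stay as they are. Present the treatment effect as the difference in change, which is the same quantity.
3. In Table 4, show raw mean (SD) change only for participants with both values.
4. For waist, say explicitly whether the same rule applies. If it does, record that the reason is the inclusion rule and that precision may fall if baseline and follow-up are closely correlated.

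The binary 5% and 10% weight-loss outcomes are outside this change, since they cannot be defined without a baseline weight.

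The cost is a few sentences in the SAP and one changed variable in the code. No new data are needed. Once the strength covariate is corrected, results do not change for any outcome without missing baselines.

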**Sample size determination**

A clinically significant effect can be achieved with 3-5 kg weight loss in obese people.[3] We assumed that WAP would increase weight loss by 2.6kg compared with usual care (WAP 3kg vs. usual care 0.4kg) for participants available for follow-up at one year, and that there would be no difference in weight loss between treatment groups for participants not available for follow-up. Assuming that 50% of participants in both treatment groups were available for follow-up at one year, the difference in weight loss between groups would be 1.3kg (WAP 1.5kg vs. usual care 0.2kg). Assuming a standard deviation of 3 in both treatment groups, and a 5% two-sided significance level, we would require 112 participants in each group to detect this mean difference with 90% power. Our estimate of 50% loss to follow-up is conservative and based on international experience in this field and existing data from similar underprivileged and highly mobile populations and interventions.

To account for potential clustering effects due to group treatment in the intervention arm, assuming a mean cluster size of 18 and an intra-cluster correlation coefficient of 0.05, a total of 208 individuals will be required in the intervention arm. The same power can be achieved with 108 in the control arm and 216 in the intervention arm which we have increased to 110 in the control arm and 220 in the intervention arm to give an allocation ratio between the two arms (2:1) which can be expressed in whole numbers. Thus we require a total of 330 individuals for the entire study

1. **DATA COLLECTION**

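### The sample size allows for clustering in the WAP arm only, the primary model assumes one ICC for groups and nurses, and no sensitivity analysis tests that assumption

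*SAP*

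**What the plan says.** **Sample size determination.** The trial is first sized without clustering: "we would require 112 participants in each group to detect this mean difference with 90% power". An inflation follows, and the reason given for it concerns one arm: "To account for potential clustering effects due to group treatment in the intervention arm". The figures behind that inflation are introduced with the words "assuming a mean cluster size of 18 and an intra-cluster correlation coefficient of 0.05". This gives 208 in the intervention arm, then 108 control and 216 intervention at 2:1, raised to 110 and 220. Nothing is added for clustering by nurse.

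**General analysis principles.** Every analysis allows for clustering by group in the WAP arm and by nurse in the control arm, and the premise is explicit: "This analysis assumes the intraclass correlation coefficient is the same between groups in the intervention arm as it is between nurses". The Kenward-Roger correction applies.

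**Analysis of primary outcome.** "The model will include a random intercept for ‘cluster’ (group or nurse, depending on treatment arm"). The Stata code has a single `|| cluster_id:` intercept, so one between-cluster variance serves both arms.

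**Elsewhere.** The sensitivity analyses for the primary outcome cover missing data, and pregnancy or bariatric surgery. Table 5 has one ICC per outcome and time point, for group and nurse together. Table 2 has a blank row for the number of groups or nurses; the number itself is not stated.

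**The concern.** The two sections start from different premises about the control arm. If the analysis premise is right and nurses cluster as much as groups, the trial has less power than stated. If the sample-size premise is right and nurses do not cluster, the primary model carries a variance estimated mainly from about 12 WAP groups (220/18 = 12.2) over to the nurse clusters. With few nurses those clusters are large, and that variance then drives the standard error.

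The two kinds of cluster also differ in nature. WAP participants share sessions that are meant to work through the group, while controls receive counselling from a nurse. The SAP gives no reason to expect equal ICCs. At stake are the width of the primary confidence interval and whether a reader could detect a failed assumption. With one pooled ICC in Table 5, a reader could not.

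**Working it through.** **1. Inputs.** All are from Sample size determination: "Assuming a standard deviation of 3 in both treatment groups, and a 5% two-sided significance level"; "the difference in weight loss between groups would be 1.3kg (WAP 1.5kg vs. usual care 0.2kg"); ICC 0.05; mean cluster size 18; 110 control and 220 intervention. The 1.3 kg is already diluted for non-attendance ("Assuming that 50% of participants in both treatment groups were available for follow-up at one year"), so it applies to all randomised participants.

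**2. The plan's own figures.**
- Unclustered: n = 2 × (1.960 + 1.282)² × 3² / 1.3² = 112 per group, as stated.
- Design effect for WAP: 1 + 17 × 0.05 = 1.85. Then 112 × 1.85 = 207.2, so 208, as stated.
- 2:1 allocation: n(control) = (1.960 + 1.282)² × 9/1.69 × (1 + 1.85/2) = 107.7, so 108 and 216, as stated.
- At 110/220: SE = 3 × √(1.85/220 + 1/110) = 0.397, power 90.6%.

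The figures reproduce with a control-arm design effect of 1, that is, a nurse ICC of 0.

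**3. Power if nurses also have ICC 0.05.** With k nurses (assumed), the control design effect is D = 1 + (110/k − 1) × 0.05, SE = 3 × √(1.85/220 + D/110), and power = Φ(1.3/SE − 1.96).

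| Nurses k | D | SE (kg) | Power |
|---|---|---|---|
| 2 | 3.70 | 0.615 | 56% |
| 4 | 2.33 | 0.516 | 71% |
| 6 | 1.87 | 0.478 | 78% |
| 10 | 1.50 | 0.445 | 83% |

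These use normal quantiles. Small-sample degrees of freedom lower them further (simulated: about 64% with 4 nurses and 71% with 6).

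**4. Calibration of the common-ICC model.** Simulation with SD 3, 12 WAP groups of 18, about 110 controls split equally among nurses, one time point, no covariates, REML and Satterthwaite degrees of freedom (equal to Kenward-Roger for one contrast when cluster sizes are equal within an arm). Full follow-up:

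| | 2 nurses | 4 | 6 | 10 |
|---|---|---|---|---|
| Group 0.05, nurse 0: SE too wide by about | 43% | 17% | 11% | 4% |
| Same: 95% CI coverage | 99.7% | 98.0% | 97.5% | 96.4% |
| Group 0.02, nurse 0.05: coverage | 95.3% | 94.3% | 94.5% | 95.0% |
| Group 0, nurse 0.05: coverage | 94.4% | 93.1% | 94.4% | 94.4% |
| Both 0.05: coverage | 96.7% | 95.4% | 95.2% | 94.9% |

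The SE percentages vary by up to about 3 points between runs. With nurse ICC 0.10 and group ICC 0.05, type I error is about 6-7%. With half the participants observed, coverage in the first scenario is 99.6%, 98.0%, 97.2% and 96.4%, and for group 0 with nurse 0.05 it is 97.6%, 95.8%, 95.3% and 95.6%.

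**5. Check by hand, 4 nurses, group 0.05, nurse 0.** The pooled ICC estimate averages about 0.035. The modelled variance factor is (1 + 17 × 0.035)/220 + (1 + 26.5 × 0.035)/110 = 0.0248. The true factor is 1.85/220 + 1/110 = 0.0175. The SE ratio is √(0.0248/0.0175) = 1.19, in line with the simulation.

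**The case against.** The assumption is stated openly, and pooling is a reasonable response when one arm has few clusters. The sample-size section is a planning simplification: it is silent on nurses rather than asserting that their ICC is zero, and allowing for nurse clustering in the analysis is the more cautious course. The remedy is also weakest where the problem is largest. With 2 nurses and both ICCs at 0.05, a model with arm-specific variances covers only 92.1%, against 96.7% for the SAP's model. If the ICCs are equal, it also loses power (about 64% to 55% with 4 nurses, 71% to 67% with 6). All of this stands, and it is why the primary model need not be replaced.

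A reader might infer more: that the interval is wrong whenever the two ICCs differ, or that the model inflates false positives. The SAP does not support either. With 10 nurses, coverage lies between 94.4% and 96.4% in the unequal-ICC rows above, and in the sample-size scenario the error costs precision, not type I error. Inflation to around 14% can be produced, but it needs nurse ICCs of up to 0.15, three times the only ICC in the SAP. Nothing in the SAP suggests that nurse counselling clusters more than group treatment.

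What the objection does not answer is that the stated 90% holds only without nurse clustering, and that nothing planned would show whether the common-ICC assumption failed.

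**Conclusion.** The point holds as an unreconciled and untested assumption. The stated 90% power rests on no clustering by nurse. Under the analysis section's equal-ICC premise, with ICC 0.05, it would be about 56% to 83% for 2 to 10 nurses. If the ICCs differ, the primary interval can be miscalibrated, and both direction and size depend on the number of nurses and on which ICC is larger. It is conservative in the SAP's own planning scenario, mildly anti-conservative if nurses cluster clearly more than groups, and mostly little affected with about 10 nurses.

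This rests on assumed nurse counts and ICC pairs, and on a simplified simulation: one time point, equal cluster sizes within an arm, no covariates. The four-visit model with covariates could give somewhat different figures.

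**What to change.** 1. Keep the common-ICC model as primary.
2. Pre-specify one sensitivity analysis of the primary outcome with separate cluster variances by arm. Replace `|| cluster_id:` by `|| cluster_id: wap ctrl, noconstant covariance(independent)`, where `wap` and `ctrl` are 0/1 arm indicators, and leave the rest of the model unchanged. Say beforehand that it will be read cautiously, or omitted, if there are too few nurses (for example 2) to estimate the nurse variance.
3. Report the ICCs separately by arm in Table 5.
4. State in Sample size determination that the 90% power assumes no clustering by nurse.

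The cost is SAP wording and one extra model. The downside is that the nurse variance will be imprecise, so the sensitivity result may have a wide interval and should not displace the primary one. In simulation at full follow-up with both ICCs at 0.05, the arm-specific model covered 95.1%, 95.4% and 95.2% with 4, 6 and 10 nurses, so it is usable once there are more than a very few.
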